#### Data management

Throughout the study the promoters will monitor the quality of the trial with special attention to protocol deviations and the quality of the data entered in the database. At the end of the trial, a meeting will be held to consider the data management report. This report will describe the different deviations from the protocol identified in each of the patients. These deviations will be classified as major or minor, and those patients with major deviations will be excluded from the protocol analysis. After the meeting, the suitability of the database for analysis will be considered, and the database will then be closed.

#### Statistical analysis plan

The statistical analysis plan will be finalized before the close of the database. This plan will include all the analysis described and others, mainly on the sensitivity of the results and the management of the missing data. In the event that in the plan of statistical analysis there is some deviation in the analysis of the main variable, an addendum to the protocol will be made. No changes will be made to the original analysis plan once the database is closed.

### Cost analysis

The procedure for determining the cost of the diagnostic test is made up of several steps: calculation of the unit cost, and accounting for all the costs associated with the test, both direct and indirect.

Calculation process: observation of the performance and accounting for all the factors involved in the procedure (units, time, number of professionals involved).

Criteria to be considered: human resources, disposable material, generic fungible supplies, pharmacy, laundry, equipment, repairs/maintenance of equipment and facilities, energy, cleaning, waste handling, rental, telephone (calls to contact subjects in follow-up), structural costs, and hospital admissions.

### Other considerations

#### Rescue

Depending on the initial endoscopic treatment carried out, a cross-over rescue treatment may be considered when the initial protocol treatment fails. For the plastic treatment group ➔ metal stent (LAMS); for the metal treatment group ➔ plastic stent. Another accepted rescue technique (only in cases of initial treatment failure) in the branch of metal stent: insertion of coaxial plastic pigtail within a LAMS.

In all these cases, the follow-up of the patients will be maintained until the end of the study according to protocol. Alternatively, if a cross-over treatment or technical variant is not possible, percutaneous surgical or radiological treatment will be offered.

#### Withdrawal

Any AE or other clinical condition of the patient which, at the clinician’s discretion, warrants withdrawal of the patient from the study; pregnancy; or expressed wishes of the patient. Withdrawal from treatment will not mean suspension of the study, given that follow-up will be maintained until the end of the study in accordance with the protocol.

The need for surgical intervention for: in these cases, patient follow-up will be ended.

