#### Follow-up

Patients will be assessed (visit, telephone call) on days 1 and 7, at 4, 8, and 16 weeks, and at 6, 8, and 12 months by personnel participating in the study, with the aim of obtaining information regarding signs and symptoms pointing to possible stent obstruction or migration, recurrence, or other AEs.

Any instances of death during the follow-up will be investigated to rule out any possible relation to the endoscopic procedure. Such occurrences will also be recorded in the CRF.

If there is clinical suspicion of obstruction or migration of the stent, an upper endoscopy will be carried out. Based on the findings of this procedure, the problem will be resolved in accordance with the directives of the intervening endoscopist. Any additional procedure or endoscopic intervention will be duly documented.

Complications will be handled and treated in accordance with the directives of the patient’s medical team. All additional tests and interventions will be duly documented.

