### Definitions

The term WON is in accordance with the literature (latest revision of Atlanta, Banks PA et al. Gut 2013) [1]. At least two imaging tests will be required (CTMD, MRI, EUS) prior to the transmural drainage, the results of which must be in agreement on the classification of the collection as WON.

Technical success is defined as the correct release of the stent at both ends, with observed drainage of the liquid.

Clinical success is defined as the significant reduction of the collection along with clinical resolution.

Recurrence is defined as a symptomatic pancreatic collection diagnosed with imaging test during the follow-up of prior procedure with initial clinical success.

AEs are defined as undesirable situations suffered by patients during the study, whether related or not to the EUS-guided transmural drainage with a stent (plastic or metal). All AEs referred by patients or observed by the medical team will be duly documented. All serious AEs will be detailed, and the study promoter/principal investigator will be notified within 7 days. In the event of a death, notification will be made within 24 h. AEs will be recorded in both the clinical history of the patient and the CRF, with appropriate medical terminology. Whenever possible, the diagnosis rather than the symptoms will be recorded. These guidelines are to be followed from the time of the signing of informed consent until 30 days after the final visit in the study calendar. AEs will be classified as mild, moderate, serious, or fatal, in accordance with the nomenclature for AEs in endoscopy (ASGE Workshops 2010, Cotton GIE 2010; 71:446–54). The determination as to whether an AE is related to the EUS-guided transmural drainage with stent (plastic or metal) will be made by the patient’s medical team, the local investigator, and the principal investigator of the study.

In Additional file 2 is included information about AE definitions and MEDDEV guidelines. “Research product security surveillance” section, according to the definitions set out in the MEDDEV 2.7/3 guidelines (rev 3, May 2015) “Guidelines on medical devices: Clinical investigations: Serious adverse event reporting under Directives 90/385/EECC and 93/42/EEC” (Additional file 2).

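### Data collection stops when a patient needs surgery, while other sections keep follow-up and adverse-event recording going; the loss depends on outcome and falls after failed stent treatment

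*Protocol article*

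**What the plan says.** Five places in the protocol article bear on what happens to data after surgery.

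- Withdrawal, last sentence: "The need for surgical intervention for: in these cases, patient follow-up will be ended". The list of indications that should follow the colon is absent.
- Withdrawal, the sentence before it: "Withdrawal from treatment will not mean suspension of the study, given that follow-up will be maintained until the end of the study".
- Rescue, after naming cross-over to the other stent and a coaxial pigtail within the LAMS: "In all these cases, the follow-up of the patients will be maintained until the end of the study according to protocol". The section then adds, as a further option, that "if a cross-over treatment or technical variant is not possible, percutaneous surgical or radiological treatment will be offered".
- Definitions, on adverse events: the recording rules apply "from the time of the signing of informed consent until 30 days after the final visit in the study calendar". Surgery is not excepted. The last contact in Table 4 is at 12 months.
- Follow-up, on deaths: "Any instances of death during the follow-up will be investigated to rule out any possible relation to the endoscopic procedure".

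The primary outcome is clinical success at 4 weeks. The secondary outcomes include clinical success at 4 months, early and late adverse events, length of stay, recurrence and cost. Handling of missing data is left to the statistical analysis plan, which is not at hand.

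**The concern.** A patient rescued with a second stent is followed to study end. A patient rescued with surgery is not. The article gives no reason for the difference. In the Rescue section surgery is reached only when the allocated stent has failed and neither cross-over nor a technical variant is possible. Leaving the data set by this route is therefore a consequence of a poor outcome. If failure or complications differ between stents, it will also be unequal between arms.

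What is at stake is mainly the later data. The Discussion makes safety one of the two questions of the trial and names severe delayed bleeding among the LAMS concerns. If sites apply the Withdrawal sentence, deaths, late adverse events, further hospital days and costs after surgery are never collected, in a group likely to be among the sickest. An analysis plan can choose how to score a known failure; it cannot restore events that nobody recorded. A second, conditional stake is the success comparison, if patients operated on before an assessment are treated as missing.

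**Working it through.** **Step 1: the texts side by side.**

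| Situation | Section | Data collection |
|---|---|---|
| Withdrawal from treatment | Withdrawal | kept to study end |
| Cross-over or coaxial-pigtail rescue | Rescue | kept to study end |
| Surgery needed, indications cut off | Withdrawal | ended |
| Adverse events, all patients | Definitions | to 30 days after the last calendar visit |
| Deaths | Follow-up | investigated while follow-up lasts |

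The direct conflict is between the third and fourth rows: for a surgical patient, one section stops data and another continues adverse-event recording past the 12-month contact. The first two rows are not contradicted, because each covers a different situation. They do show that surgery is handled differently from the other ways of leaving allocated treatment.

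**Step 2: the plan's own sample size.** Inputs from the Sample-size calculation section: success 0.75 (LAMS) and 0.50 (plastic), 57 per arm, 80% power, type-I error 5% (two-sided assumed), 5% loss.

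With a mean proportion of 0.625,
n = [1.960 × √(2 × 0.625 × 0.375) + 0.842 × √(0.75 × 0.25 + 0.50 × 0.50)]² / 0.25² = 57.7, or 58 per arm before loss. The unpooled formula gives 54.9, and 54.9/0.95 = 57.8, or 58 with loss. The stated 57 is reproduced to within one patient; power at 57 per arm is 79.5%. The point here does not depend on that figure. The loss allowance is 0.05 × 114 = 5.7, about six patients in all.

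**Step 3: what would happen to the primary comparison if early surgical patients were dropped.** The documents give no surgery rates, so the shares s below are assumptions. Every dropped patient is taken to be a failure. The observed success rate is then p/(1 − s), in 57(1 − s) patients.

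| Assumed share before week 4, LAMS / plastic | LAMS | Plastic | Difference (points) | Power |
|---|---|---|---|---|
| none dropped | 75.0% | 50.0% | 25.0 | 79.5% |
| 5% / 10% | 0.75/0.95 = 78.9% | 0.50/0.90 = 55.6% | 23.4 | 73.3% |
| 5% / 15% | 78.9% | 0.50/0.85 = 58.8% | 20.1 | 60.0% |
| 5% / 5% | 78.9% | 0.50/0.95 = 52.6% | 26.3 | 83.3% |
| 10% / 5% | 0.75/0.90 = 83.3% | 52.6% | 30.7 | 93.3% |

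The rise in an arm is p × s/(1 − s), so it depends on the success rate as well as on the surgery share. With 5% surgery under LAMS the rise is 0.75 × 0.05/0.95 = 3.9 points. With 7% under plastic it is 0.50 × 0.07/0.93 = 3.8 points. The arm with more surgery is therefore not always the one inflated more, and equal shares already widen the difference.

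With no true effect (50% in both arms) and 10% surgery in one arm only, that arm shows 0.50/0.90 = 55.6%, a spurious difference of 5.6 points.

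**The case against.** The case against a stronger statement is good, and most of it stands.

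- *Scope.* A reader might infer that every patient who has surgery leaves the study. The sentence breaks off before its indications, so it may cover only some of them, possibly including surgery unrelated to drainage. The link from surgery to failed drainage is supported only for the last-line option in Rescue.
- *Contradiction.* A reader might infer that the plan breaks its own rule to follow everyone. No such rule exists. The two retention sentences concern withdrawal from treatment and stent rescue, and the one in Rescue comes before the surgical option. The surgery line can be read as an intended exception. The true conflict is with the adverse-event window in Definitions.
- *Primary outcome.* A reader might infer that surgical failures drop out of the 4-week and 4-month results. Nothing says so. Such a patient can be scored as a failure without another visit, and missing data belong to the analysis plan. Additional comments also places the change of strategy for lack of short-term success after the 4-week control, when the primary outcome is already recorded.
- *What is recorded.* The event leading to surgery, and the surgery itself, should be captured: Additional comments and Follow-up both require interventions and additional procedures to be documented. Only the period after surgery is exposed. Mortality is not listed as an outcome by name; it enters through safety, where Definitions has a fatal grade.

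What this does not answer is the loss of later data. If the line is a deliberate exception, it still removes information after a failure-related event. Its missing indications leave nine centres to decide for themselves when it applies.

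**Conclusion.** The point holds in limited form. As written, the Withdrawal sentence ends data collection for patients who need surgery, for indications that cannot be read. It conflicts with the adverse-event window in Definitions and differs from the handling of other departures from treatment. Because surgery can follow failed stent treatment, the resulting loss of deaths, late adverse events, hospital stay and costs depends on outcome and may be unequal between arms. That loss follows directly from the text and cannot be repaired at analysis. Its size cannot be estimated, since no surgery rate is given.

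Bias in the 4-week and 4-month success comparisons is a risk and not a stated rule. It arises only for surgery before the assessment, and only if those patients are treated as missing. In the three cases with unequal shares the planned 25 points becomes 23.4, 20.1 or 30.7. These figures rest on assumed surgery shares, on the planned success rates, and on all surgical patients being failures. They show that the bias can go either way, and they do not predict it.

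**What to change.** Reconcile Withdrawal, Rescue and Definitions in a short amendment:

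- Replace the sentence that ends follow-up at surgery with one that keeps these patients in the scheduled data collection (adverse events, death, hospital stay, cost) to 12 months, unless consent is withdrawn.
- State that surgery for failed drainage or a procedure-related complication before the 4-week or 4-month assessment counts as clinical failure at that assessment, and not as missing.

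The cost is the amendment and a few extra visits, calls or record checks, on dates already in Table 4, for what is likely to be a small number of patients. Only data collection and scoring change; when surgery or any other rescue is used is left as it is.

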### Ethical aspects and confidentiality

The protocol will be approved by the CEIC of each participating hospital as well as that of the coordinating center (HUB). The study researchers will carry out their tasks in compliance with ethical principles of clinical research established in the Declaration of Helsinki, and with the norms of Good Clinical Practices. It is planned to hire a policy to cover the concepts and compensations according to current legislation (RD 1591/2009) that regulates clinical investigation with healthcare products. Before starting the clinical trial, it is planned to request authorization of the Spanish Agency for Medicines and Health Products (AEMPS) and the CEICs. Before inclusion of the patient in the trial, a written informed consent will be requested. In relation to the study data we will follow the provisions of Organic Law 15/1999 of 13 December on “Protection of Personal Data.”

### Publication of results

There is a commitment to publish the results of this study in high-impact international journals, should the results be of sufficient scientific interest. However, no patient names will appear in any article, and no one, with the exception of the researchers in this study and the members of the Hospital Ethical Committees, will have access to the data, in accordance with the Law on the Protection of Data of a Personal Nature.

## Discussion

Although open surgical necrosectomy has been the traditional treatment of choice in patients with infected or symptomatic pancreatic necrosis, other minimally invasive techniques have been developed in recent years (endoscopic necrosectomy, guided radiological percutaneous drainage, and retroperitoneal treatment) for treating collections, so as to improve on the high morbidity and mortality rates of traditional surgical treatment [3, 21–23].

At present, endoscopic transmural drainage plus endoscopic necrosectomy represents a viable technique that is reasonably safe and effective when carried out in centers that have experience in doing so. Although each of these is a minimally invasive endoscopic technique, they are not entirely free of complications, the most common of which are bleeding, perforation, post-procedural infection, and stent migration [7, 24]. Additionally, with the continuous technological advances being made and the appearance of new materials for endoscopic use, doubts have arisen as to which devices are best to use. One clear example of this uncertainty is the choice of stent. To date, most published studies on guided transmural drainage with endoscopy have involved double pigtail plastic stents, with the number and diameter varying depending on the collection type [23, 24]. In the past years, some reports have been published on the use of self-expanding covered metal stents offering greater diameter, and therefore greater volume in the drainage of the collection [25–27]. However, both types of stent are intended for bile drainage and are not expressly designed for transmural drainage of abdominal collections, so more dedicated stents were investigated [8].

Recently, LAMS designed for the drainage of pancreatic collections have appeared with demonstrated efficacy in a number of studies but they are also more costly [16–20]. These stents are totally covered and offer a maximum caliber of 15–20 mm, thereby allowing for endoscopic necrosectomy in repeated sessions without the need for replacement. In our experience, they permit transmural drainage of pancreatic collections and endoscopic necrosectomy if it is needed, they are safe and effective, and they reduce the duration of the procedure [10, 28].

However, with the increasing use of these stents, significant LAMS-related AEs (i.e., severe delayed bleeding, buried stent syndrome, obstruction, migration) have been reported in several papers.

To date there is only one comparative prospective study of self-expanding LAMS type metal stents, versus plastic stents in the endoscopic treatment of WON-type pancreatic collections, and it concluded that there were no significant differences in treatment outcomes between the two. In order to minimize LAMS-related AEs, they recommend follow-up imaging and LAMS removal at 3 weeks if collection is resolved [29].

The PROMETHEUS trial is supported by the Spanish Society of Digestive Endoscopy and includes nine tertiary centers, as well as experts in the management of WON. Hospital Universitari de Bellvitge has the leadership and main role in centralizing the decisions in case of doubts and controversies, and in limiting heterogeneity.

In conclusion, this randomized multicenter trial is necessary and essential in the effort to clarify the safety and theoretical superiority of LAMS in the management of WON, compared with plastic stents.

### Trial status

*Protocol of submitted version, number and date*: number 2.1; date June 2018

*Recruitment*: Start date 27 June 2017 and recruitment will be completed by June 2020

*Revision chronology*:
a-*PROMETHEUS, June 2017, original: version 1,* first draft of the study protocol.b-*PROMETHEUS, September 2017, amendment n° 1: version 2.*
Main amendments: (1) to clarify the second inclusion criterion – in case of more than one collection, the EUS-guided drainage will be limited to *only one* pancreatic collection (WON), related to the symptomatology (Table 2); (2) addition of the “Research product security surveillance” section, according to the definitions set out in the MEDDEV 2.7/3 guidelines (rev 3, May 2015) “Guidelines on medical devices: Clinical investigations: Serious Adverse event reporting under Directives 90/385/EECC and 93/42/EEC” (Additional file 2); (3) extension to nine centers with respect to the initial protocol (four centers); (4) procedural technique, rescue section: in case of failure, adding of the possibility of a “Technical variant” in LAMS group – an insertion of coaxial plastic pigtail within the metal stentAdditional changes: (1) addition of new and relevant references; change of the grading of the AE classification (immediate, early, and late); (2) commercial name of each stent; (3) start delayed, from the beginning of 2016 to June 2017; (4) procedural technique section: additional comments regarding when and how some technical variants can be made; and technical notes about necrosectomy technique; (5) data management paragraph in the statistical section; and (6) telephone call at 7 days, and additional new legend explaining the possibility of a second imaging procedure at 8 weeks, only in case of radiological clinical success but with persistence of the collection > 5 cm (Table 4, Timeline)c-*PROMETHEUS, June 2018, amendment n°2: version 2.1 – definitive*
Minor changes: addition of a new size of LAMS (20 mm in diameter).AEMPS and CEIC have been notified after every amendment, with acceptance by each institution

## Data Availability

Minimal dataset necessary to interpret the findings available from the corresponding author on reasonable request.

## Abbreviations

AE: Adverse event
AEMPS: Spanish Agency for Medicines and Health Products
ASA: American Society of Anesthesiologists’ classification
CEIC: Clinical Research Ethics Committee
CRF: Case report form
CTMD: Computed tomography multidetector
EUS: Endoscopic ultrasound
LAMS: Lumen-apposing metal stent
MRI: Magnetic resonance imaging
SEED: Spanish Society of Digestive Endoscopy
WON: Walled-off necrosis
